###### Genogram

At the beginning of the medical interview, over 15 min, the clinician will produce a genogram, which aims to represent the participant’s family on three generations and to highlight the relationships between the adolescent and each member of these three generations. During this interview, the clinician will also search for a pre-existing personal and family psychiatric condition, and ask the patient about his or her hobbies, professional project, and romantic relationships. This introductory time also aims to allow the participant to feel safe and confident in this unknown context of clinical evaluation.

###### MINI International Neuropsychiatric Interview for Children and Adolescent (M.I.N.I. Kid 7.0.2)

The MINI International Neuropsychiatric Interview (51) is a brief structured diagnostic interview developed by American and European psychiatrists and clinicians. Although it can also be used as a self-assessment questionnaire, it lowers its psychometric performances, which is why we chose to use it as a clinician-administered questionnaire.

The MINI Kid, which is dedicated to children and adolescents, explores the most frequent and most relevant disorders in child psychiatry: mood disorders, suicidality, anxiety disorders and PTSD, addictions, motor disorders, hyperactivity, behavioral disorders, eating disorders, and psychotic disorders.

David V. Sheehan, as “copyright holder” of the all versions of “MINI International Neuropsychiatric Interview for Children and Adolescents - M.I.N.I. Kid 7.0.2 (8/8/16 version),” granted permission to [name]-PhD in CHU Brest (France), as healthcare providers, to use this interview under terms and conditions which we respected.

###### Psychoactive Substances Use

To complement the MINI Kid, we will use eight close-ended questions to explore whether the psychoactive substances use has changed or not since the attack. We will focus in particular on alcohol, tobacco, and cannabis, which are the most frequently used substances in the age group of the target population.

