## Methods and Analysis

### Design

This study, which will be the first step of the AVAL cohort study, will be a monocentric cross-sectional observational study. It will be performed in a single center, 12 to 15 months after the terrorist attack to which the target population was exposed.

The evaluation will consist of both self-assessment questionnaires and clinician-administered questionnaires. Both these evaluations will last around 1 h and will be performed on distinct days. The hetero-evaluation will be conducted by the same investigator for all participants. Nevertheless, in order to provide a safe space for all students and their families, and prevent any emotional difficulty, volunteers from the medico-psychological emergency cell (*CUMP-29 renforcée*) will be seconded to assist the investigator during all data collection.

Pre-existing personal and family psychiatric condition, family composition, psycho-traumatic history, stressful life events, characteristics of traumatic exposure, early evolution of disorders, and health care pathway since the attack will be explored retrospectively upon the participant’s statement. Psychological symptoms and psychiatric disorders will be assessed based on the current health status of participants at the time of evaluation.

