##### Clinical Assessment 1 Year After the Attack: Medical Interview and Clinician-Administered Questionnaires

All the questionnaires will be administered by the same clinician who is a psychiatry resident (8th year of medical school) supervised by a child and adolescent psychiatrist, and a military psychiatrist who are both trained in psycho-traumatology and have professional experience in this field.

Exceptionally, volunteers from the medico-psychological emergency cell will be seconded to assist the investigator during data collection. Two volunteers will be present each day. One of them will be present during the medical interviews in order to be able to offer the participant a space for dialogue at the end of the interview if necessary, while the second one will be on standby in the high school and welcome any person (student, family, teachers, etc.) who would feel the need to come and talk about the attack.

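### The eight questions on change in alcohol, tobacco and cannabis use are asked face to face with a volunteer present, which risks under-disclosure; the existing self-assessment session could carry them (minor)

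*Protocol article*

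**What the plan says.** The Psychoactive Substances Use section of the Protocol article says "we will use eight close-ended questions to explore whether the psychoactive substances use has changed or not since the attack", and adds: "We will focus in particular on alcohol, tobacco, and cannabis". The section stands under the heading "Clinical Assessment 1 Year After the Attack: Medical Interview and Clinician-Administered Questionnaires". The opening text of that block fixes the mode: "All the questionnaires will be administered by the same clinician who is a psychiatry resident". It also fixes who else is there. Two emergency-cell volunteers attend each day, and "One of them will be present during the medical interviews in order to be able to offer the participant a space for dialogue". The other is on standby elsewhere in the school.

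The Design section describes two parts: "The evaluation will consist of both self-assessment questionnaires and clinician-administered questionnaires". On their timing it says: "Both these evaluations will last around 1 h and will be performed on distinct days".

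A reason for having the clinician ask the questions is given once, in the MINI Kid section: "Although it can also be used as a self-assessment questionnaire, it lowers its psychometric performances". No reason is given for the eight added questions.

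**The concern.** Tobacco, alcohol and cannabis are subjects on which adolescents may not answer openly to adults. Here the questions are put by a psychiatry resident with a second professional present. That professional comes from the emergency cell which, according to the Introduction and the Post-Immediate Evaluation section, saw most of these students soon after the attack. The consent statements show that participants include minors.

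The questions are closed, so they do not need a clinician to elicit an answer, and a self-completed session is already planned. The article itself, under Psychiatric Disorders Following Traumatic Exposure, cites studies that found more substance use among adolescents after attacks. A student who conceals use will also conceal a change in it, so the result would drift towards no change, away from what the cited literature leads one to expect. The limitations in the Discussion cover anniversary, media and group effects. They do not mention under-reporting or the presence of others at the interview.

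**Working it through.** The document gives no figure to reproduce. The check is a reading of the sections side by side, followed by an illustration on assumed values.

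**1. Mode and setting.** The eight questions fall in the clinician-administered block, all of whose questionnaires are put by one clinician, with one volunteer present during the interviews. Since the other volunteer is the one waiting elsewhere, being present naturally means being in the room.

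**2. Reason for the mode.** The MINI Kid section defends clinician administration by the loss of psychometric performance when that instrument is self-completed. This concerns a structured diagnostic interview and does not carry over to eight added closed questions.

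**3. Alternative already in the plan.** The self-assessment lasts about 1 h and takes place on a different day. It already holds added closed questions: eight on family and school resources and three on school performance. For both sets the article says that the answers will be set against the interview data. The same arrangement would suit the substance-use items.

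**4. Which result depends on these items.**
- Primary endpoint (PTSD prevalence): self-completed PCL-5. Not affected.
- Prevalence of addictions, named in the Aims: the diagnostic instrument that covers addictions is the MINI Kid, which is given in the same interview. It is exposed to the same risk, and moving the eight questions does not change that.
- Change in use since the attack: the eight questions are the only items described for it. This is the result at stake.

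**5. Size, on assumptions only.** Let p be the true proportion whose use increased and d the proportion of those who disclose it, with no false positives. Then reported proportion = p × d. The document gives neither p nor d.
- p = 30% of the 53 students (53 × 0.30 = 15.9): d = 90% gives 0.30 × 0.90 = 27% (14.3 students); d = 75% gives 22.5% (11.9); d = 60% gives 18% (9.5).
- p = 20%: d = 95%, 80% and 60% give 19%, 16% and 12%.

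These figures show the loss against full disclosure. They do not show the gain from moving the items, which is p × (d in self-assessment − d in interview). With p = 30%, 90% in self-assessment and 75% in the interview, the gain is 0.30 × 0.15 = 4.5 percentage points, or 53 × 0.045 = 2.4 students. If disclosure is the same in both settings, the gain is zero.

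**The case against.** The strongest reply is that the plan contains no error here: it states a mode of administration clearly, and another is preferred. The interview also serves the aim of finding and referring students who need care, it opens with 15 minutes meant to put the participant at ease, and care pathways are likewise explored with closed questions in it. This stands in part. The point is an inexpensive improvement and not the correction of a contradiction. The introduction builds trust, but it does not give privacy.

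Several stronger readings are tempting and are not supported.
- A reader might infer that the addiction prevalence in the primary aim is biased by the way these eight questions are asked. The instrument that diagnoses addictions is the MINI Kid; the eight questions only supplement it.
- A reader might infer that the comparison by PTSD status is distorted. The Statistical Analysis section plans comparisons of baseline characteristics and correlations with factors that may contribute to PTSD, and does not name change in substance use in either.
- A reader might infer that disagreement between self-report and interview would measure concealment. Once the items are moved, the interview holds no second standardised measure of change in use. A student can also drink more without having a disorder, so a mismatch with the MINI Kid proves nothing.
- A reader might infer that substance use is the only sensitive topic handled in this way. Suicidality, romantic relationships and psychiatric history are also asked in the interview.

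Two further objections stand. The article does not describe how private the self-assessment is, and the Design section has volunteers assisting throughout data collection, so privacy must be arranged and cannot be taken for granted. Also, 15 months after March 2017 is June 2018, and the article reports a presentation of the protocol in November 2018. The mode for this wave may therefore no longer be open to change.

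**Conclusion.** The point holds as a minor one. Asking the eight questions face to face with a volunteer present creates an avoidable risk of under-disclosure, and the plan's stated reason for clinician administration does not cover them. The effect is confined to the supplementary result on change in use. It leaves the PCL-5 endpoint untouched, and the exposure of the MINI Kid addiction diagnoses is the same with or without the change.

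That adolescents disclose less in this setting is a methodological inference; the document neither quantifies nor rebuts it. The expected direction is towards no change, because concealment hides decreases as well as increases; it is downward only if the reported result is increased use. The size cannot be derived from the document, and the illustrative percentages rest wholly on assumed values.

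**What to change.** Move the eight questions into the existing self-assessment session, to be completed individually and out of view of classmates and staff. Name the self-completed answers as the reported result for change in use. Leave the MINI Kid and the volunteer arrangement as they are. Let the clinician go over the answers in the interview, as is already planned for the resource and school-performance items, without replacing the recorded self-report. Add one sentence to the limitations saying that the MINI Kid addiction module may be under-reported.

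The cost is a few more minutes of self-assessment, a few fewer in the interview, and no clinician at hand to clarify an item while it is being answered. No extra staff or visit is needed. If data for this wave have already been collected, what remains is a limitation sentence covering the eight questions as well, and the change of mode for any later step of the cohort.

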###### World Health Organization Disability Assessment Schedule 2.0

In order to explore any functional impairment, the World Health Organization Disability Assessment Schedule 2.0 (WHODAS 2.0), which was developed in connection with DSM-5 (49), will be used to measure health and disability through six areas of daily life: cognition, mobility, self-care, getting along/interacting with other people, life activities, and participation (joining in community activities). As a generic instrument, WHODAS 2.0 can be used to measure the functional impact of any pathology. The full version consists of 36 questions, but we chose to use the short version administered by an investigator, which brings together 12 items. These 12 questions explore the operational difficulties experienced over the last 30 days in the six areas detailed above. The 12-item short version explains 81% of the variance of the long version.

###### Psychological and Medical Care

To conclude the medical interview, the clinician will explore the psychological and medical care that the participant may have sought and/or received since the attack. Using nine questions (eight close-ended and one semi-open), we will explore the health care pathway followed by the participant since the attack, providing information about the types of medical and/or psychological care the patient received (medical/psychiatric/psychological care, psychotherapy/medication), when (during the first week following the attack or not) and where (type of healthcare structure).

If the participant did not seek any psychological or medical care, the clinician will notify why (the participant didn’t want to, the participant’s parent or legal guardians didn’t want him/her to, the participant didn’t feel like he or she needed help, the participant or his/her legal guardians didn’t know where to go to get help, the participant or his/her legal guardians thought it was too soon to get help, other reason).

Finally, to limit the clinical bias in our evaluations, we will notify any current medication.

#### Statistical Analysis

Descriptive statistics of the population will include the number of missing data, the mean, the standard deviation, the median, the minimum, and the maximum for continuous variables, as well as frequency and percentage for qualitative variables.

The baseline characteristics of the sample will be compared between adolescents who did or did not develop PTSD using comparison of means (Student test or Wilcoxon test) or of frequencies (Chi-square test or Fisher’s exact test).

Analysis of correlation will also be performed in order to investigate whether some of the factors we evaluate might play a role in the development of PTSD.

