#### Exclusion Criteria

We will exclude from this study the three students who were physically wounded during the attack and, therefore, didn’t have the same sensorial exposition. However, if they want to, these three teenagers will be offered the same standardized assessment as all participants, so that we can fulfill our aim of clinical screening and refer them to specialized care if necessary.

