###### Post-Traumatic Stress Disorder Check-List for DSM-5

The Post-traumatic stress disorder Check-List for DSM-5 (48) consists of 20 items which explore the 20 symptoms of PTSD described in the DSM-5 (49). For each symptom, the patient evaluates the intensity of the symptom during the previous month on a 5-point Likert scale from 0 (not at all) to 5 (extremely). The 20 items can be grouped into four subscales corresponding to the four sub-syndromes of PTSD: intrusion symptoms (items 1 to 5, corresponding to criterion B), avoidance symptoms (items 6 and 7, corresponding to criterion C), negative of cognition and mood (items 8 to 14, corresponding to criterion D), and hyperarousal (items 15 to 20, corresponding to criterion E).

This self-questionnaire allows to obtain a total score of severity (by adding the score obtained for each of the 20 items) or an independent severity score for each criterion from B to E. It can also be used as a diagnostic scale, which is how we will use it: the diagnosis of PTSD will be retained when the global severity score > 32 (48). The prevalence of PTSD 12 to 15 months after the attack, assessed using PCL-5, will be the primary endpoint of this study.

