Despite these strengths, our study is subject to several limitations. First, due to the cross-sectional design of the study, we will not be able to establish causal relationships. Second, with a target population of only 53 individuals, the number of patients will necessarily be limited. Third, the data collected through the post-immediate evaluation was gathered outside of any protocol at that time, which makes it barely scientifically exploitable. This initial data is thus very different from the one we will collect 12 to 15 months after the attack, which will not allow us to compare them.

Fourth, although the home and school environment seem to play a key role in modulating children’s and adolescents’ reaction to terrorism (7, 29, 52–54), our evaluation of this environment will be superficial. It would be interesting to conduct a real systemic assessment among these adolescents including interviews with their teachers and families, but unfortunately this cannot be done as part of this study.

Finally, it seemed to us that collecting data for this study 1 year after the terrorist attack would increase our chances of including most of the target population while minimizing the risks of disruption for the students and their families, since they would probably already be thinking about the event. However, the choice of this date could be a source of bias. Indeed, it is possible that the symptoms of post-traumatic stress, depression, and anxiety are more important around the first anniversary of the traumatic event.

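### For the PTSD risk-factor aim, the only analysis specified compares cases with non-cases; the PCL-5 total score, already collected, should be the outcome

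*Protocol article*

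**What the plan says.** The Aims section makes it a secondary aim to identify factors associated with the risk of PTSD, anxiety disorders or depressive disorders 12 to 15 months after the attack.

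The section on the PCL-5 notes that "This self-questionnaire allows to obtain a total score of severity", and then chooses the diagnostic use: "the diagnosis of PTSD will be retained when the global severity score > 32". The prevalence on that definition is the primary endpoint.

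The Statistical Analysis section contains two association analyses. In the first, baseline characteristics are "compared between adolescents who did or did not develop PTSD using comparison of means (Student test or Wilcoxon test) or of frequencies" (chi-square or Fisher's exact test). The second, also about PTSD, is one sentence that begins: "Analysis of correlation will also be performed in order to investigate whether some of the factors we evaluate might play a role". It does not say whether PTSD enters as a status or as a score, which coefficient is used, or which factors are examined.

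The Discussion concedes that "with a target population of only 53 individuals, the number of patients will necessarily be limited" and that causal relationships cannot be established.

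**The concern.** The PCL-5 total is available for every participant who completes the questionnaire. The one association analysis with a stated method uses only whether a participant is above or below the cut-off. Someone just over it counts the same as someone far over it, and someone just under it the same as someone with no symptoms. Recruitment cannot make up for that loss, because the population is fixed.

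The practical risk is that real associations are missed. In addition, the battery supplies many possible factors. If each is tested at the usual level and the results are not marked as exploratory, some chance findings are likely to be read as risk factors. The Discussion intends the epidemiological results to inform response strategies after future attacks.

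**Working it through.** The article gives no sample-size, power or significance-level figure, so there is nothing to reproduce. The inputs are as follows.

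- **N:** 53 students are the target population, and "We will exclude from this study the three students who were physically wounded during the attack". The text does not settle whether the three are among the 53, so N is at most 50 or 53. I use 50; 53 changes little.
- **Prevalence p:** none is stated for this sample. The Introduction cites 1% to 60% across studies. I assume 10% to 50%.
- **True correlation and test level:** assumed, with two-sided 5% per test.

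**1. Information kept after the split.** For a normally distributed score cut so that a fraction p lies above, the fraction kept is φ(c)² / [p(1−p)], with c = z(1−p).

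| p | kept | lost | 50 adolescents act like |
|---|---|---|---|
| 10% | 0.342 | 66% | 17 |
| 20% | 0.490 | 51% | 24 to 25 |
| 25% | 0.539 | 46% | 27 |
| 30% | 0.576 | 42% | 29 |
| 50% | 0.637 | 36% | 32 |

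**2. Power for one factor, true r = 0.35, n = 50.** By Fisher's z, power ≈ Φ(√(n−3) · atanh(r) − 1.96).

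- Total score: √47 × atanh(0.35) = 6.856 × 0.3654 = 2.505; Φ(0.545) = 0.71.
- Split at p = 20%: r shrinks by √0.490 = 0.700 to 0.245; 6.856 × 0.2501 = 1.714; Φ(−0.246) = 0.40.
- Split at p = 25%: r shrinks by √0.539 = 0.734 to 0.257; 6.856 × 0.2628 = 1.802; Φ(−0.158) = 0.44.

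Simulation (10,000 runs per setting) over a wider range, n = 50:

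| true r | total score | split, p = 10% | 20% | 30% | 50% |
|---|---|---|---|---|---|
| 0.3 | about 58% | 23% | 31% | 37% | 39% |
| 0.4 | about 84% | 37% | 51% | 60% | 64% |

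**3. What the two-group test can detect.** The standardised difference detectable with 80% power is (1.96 + 0.84) × √(1/n₁ + 1/n₀). With n = 50 this is 1.32 at 10% prevalence (5 against 45), 0.99 at 20% (10 against 40) and 0.86 at 30% (15 against 35).

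**4. How many candidate factors.** The article does not list the factors to be tested, so this is my count from the instruments.

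- Narrow count, 13: six socio-demographic items, personal and family psychiatric history (2), LEC-5, two ALCES periods, EPS-10 and PDI.
- Adding the PDEQ and four early items (school absence, medication, rated impact, certificate) gives 18.
- Adding the 11 immediate and 7 post-immediate symptoms gives 36.
- Adding the eight family and school questions gives 44.

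If no factor mattered and the tests were independent, the chance of at least one result at 5% is 1 − 0.95^k: 49% (k = 13), 60% (18), 84% (36) and 90% (44). Correlation among factors lowers it. By simulation with a common correlation of 0.3 it is 54% at k = 20 and 75% at k = 40; with 0.5 it is 42% and 57%.

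**The case against.** **The correlation analysis may already use the total score.** This is a fair reading, and a reader who infers that the score is discarded altogether goes further than the text. What stands is that the scale is unstated, that the sentence is framed around the development of PTSD, and that the PCL-5 section announces diagnostic use. The Statistical Analysis section does not even say that PTSD status comes from the PCL-5 rather than the MINI Kid; I infer it from the primary endpoint.

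**Comparing cases with non-cases fits the aim and the endpoint.** It does, and as a descriptive table it should stay. It is a weak basis for finding associated factors in a population of this size.

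**The multiplicity rule, covariate list and adjusted model may sit in a full protocol or analysis plan.** Agreed. An article commonly leaves these out, so I do not count their absence as a fault.

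**A larger multiplicity problem could be claimed.** Counting every item, including nine care questions, gives 53 variables and 1 − 0.95^53 = 93%. That is not supported. Care since the attack is not a baseline characteristic, the Discussion itself regards the early data as of little scientific use, and independence is implausible for these factors.

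**Adjusting for several factors would eat up the gain.** Only in part. At the first Holm step for four factors (level 0.0125), r = 0.35 and n = 50, power is Φ(2.505 − 2.498) = 0.50 with the score. With the split it is Φ(1.714 − 2.498) = 0.22 to Φ(1.802 − 2.498) = 0.24. Both fall, and the score keeps its advantage. Adjusting for correlated covariates would cost something further.

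**The limits are already acknowledged.** The small number and the lack of causal inference are. Loss of information and chance findings are not mentioned.

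**Conclusion.** The point holds for the choice of outcome scale in the PTSD association analysis. The only fully specified method rests on case status, and the severity score has no stated role as an outcome. The loss is about 36% to 66% of the information over 10% to 50% prevalence. It is tempting to say that half is lost, but that holds only around 15% to 30% prevalence, which the article does not give. At r = 0.35 and n = 50, power drops from about 0.71 to 0.40-0.44 at 20-25% prevalence.

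These figures assume a roughly normal underlying score, a test at 5% and the stated correlations. A skewed score would change them.

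The chance-finding figure of about 49% to 90% depends on what is counted and assumes independence, so it is lower in practice. It supports labelling the results as exploratory and nothing stronger. The primary prevalence estimate and its cut-off are unaffected.

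**What to change.** 1. Keep PCL-5 above 32 for the primary prevalence estimate, and keep the two-group comparison as a descriptive table.
2. State that the PTSD association analysis uses the PCL-5 total score as its outcome, by correlation or by linear regression with robust or bootstrap intervals.
3. Name a short list of four or five factors that the article already cites in its section on risk factors, for example sex, prior psychiatric history, prior trauma, peritraumatic distress (PDI) and social support (EPS-10).
4. Label every other association test exploratory, and report effect sizes with intervals.

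The cost is a few sentences and a little more analysis; no new data or visits are needed. There are two drawbacks. Effects are expressed in score points and not as odds of being a case. And the change does nothing for the anxiety and depressive disorder outcomes in the same aim, for which the MINI Kid gives diagnoses.
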